### Intervention

TXYF granule or placebo will be orally administered one packet (strength, 8.1 g) after dissolved twice a day (1 h after the meal) for 12 weeks. Over the course of the study, participants are required to discontinue therapeutic medications associated with IBS-D. Simultaneously, probiotic foods, functional foods, and dietary supplements are also prohibited. Participants are obligated to fill in the study diary daily involving medication administration record, concomitant treatments, and dietary questionnaire which avail to check compliance and statistically rectify dietary bias. Onset of exacerbated IBS-D symptoms allows rescue medications for less than 1 week, which needs to be documented in the electronic Case Report Form (eCRF).

### Colonoscopy and biopsies

Participants who did not have a colonoscopy 1 year prior to enrollment will undergo colonoscopy and sigmoid mucosal biopsy (week 0) for assessment of microscopic colitis, from which 10 participants of each group will be randomly selected to undergo mechanistic assessment and 2 additional samples of sigmoid mucosa will be obtained. After 12 weeks of treatment, these 20 participants will undergo a second colonoscopy and two sigmoid colon biopsies (week 12). Besides, 10 healthy subjects will be recruited to undergo colonoscopy and two sigmoid colon biopsies. The obtained samples will be promptly snap-frozen in liquid nitrogen and then stored at − 80 °C for the next-generation high-throughput RNA sequencing (RNA-seq) and quantitative real-time PCR (qRT-PCR). Samples of intestinal mucosa will be destroyed after use.

### RNA isolation, library preparation, and sequencing

According to the manufacturer’s instructions, total RNA will be isolated from sigmoid colon samples using TRIzol (Life Technologies). RNA purity, concentration, and integrity by using the NanoPhotometer spectrophotometer (IMPLEN, CA, USA), Qubit RNA Assay Kit, and RNA Nano 6000 Assay Kit respectively will be measured. Two to 3 μg total RNA per sample as input material is needed for cDNA library construction and subsequent PCR amplification and library quality will be evaluated lastly on the Agilent Bioanalyzer 2100 system. RNA-seq will be conducted on an Illumina Hiseq 2000 platform.

### RNA-seq data processing and bioinformatics analysis

Raw data of fastq format through quality control including removing a series of hybrid reads and low-quality reads will be filtered as clean data. Clean data then will be mapped to the human reference genome employing HISAT2 v2.0.4 and the aligned reads per sample will be assembled by StringTie (v1.3.3). Both ncRNAs and coding transcripts will be normalized and expressed as fragments per kilo-base of exon per million fragments mapped (FPKM). Differential expression will be analyzed by using Cuffdiff. Gene Ontology (GO) and Kyoto Encyclopedia of Genes and Genomes (KEGG) enrichment analysis of differentially expressed genes will be implemented by GOseq R package and KOBAS software, respectively. To predict the targets of ncRNAs, databases including TargetScan (www.targetscan.org), starbase (http://starbase.sysu.edu.cn/), deepbase2.0 (http://deepbase.sysu.edu.cn/), and circInteractome (https://circinteractome.nia.nih.gov) will be used. Visual networks of ncRNAs and mRNAs will be constructed by Cytoscape software.

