### Mechanistic outcome

We will analyze the whole transcriptome profiling of intestinal mucosae from the TXYF granule group (*n* = 10) and placebo group (*n* = 10) at baseline and week 12 and healthy subjects (*n* = 10) at baseline. The whole set of transcriptional deviations including mRNA, miRNA, lncRNA, circRNA, and functional networks of ncRNAs and mRNAs in IBS-D will be disclosed, which makes us to seek for the underlying molecular mechanisms and find out specific diagnostic biomarker. Meanwhile, therapeutic targets and pathways about TXYF in IBS-D will be clarified. On an Illumina Hiseq 2000 platform, the preparation of whole-set transcriptome libraries and deep sequencing will be executed by Novogene Bioinformatics Technology Cooperation (Beijing, China).

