#### Mechanistic data analysis

The differential expression analysis about mRNA, miRNA, lncRNA, and circRNA for all pairwise comparisons: IBS-D patients versus healthy controls, TXYF granule (pre-treatment) versus placebo (pre-treatment), TXYF granule (post-treatment) versus placebo (post-treatment), TXYF granule (pre-treatment) versus TXYF granule (post-treatment), and placebo (post-treatment) versus placebo (post-treatment), will be performed by Cuffdiff. An adjusted *P* < 0.05 (Student’s *t* test accompanied with Benjamini-Hochberg FDR adjustment) will be used as the cut-off for significantly differentially expressed genes. Pearson correlation test will be used for target gene prediction.

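### The FPKM and Cuffdiff route fixed for noncoding RNA does not validly quantify circRNA or miRNA, two of the four RNA classes in the mechanistic outcome

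*Protocol article*

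**What the plan says.** The Mechanistic outcome section of the protocol article covers four classes of RNA: "The whole set of transcriptional deviations including mRNA, miRNA, lncRNA, circRNA, and functional networks of ncRNAs and mRNAs in IBS-D will be disclosed". Mucosa comes from 10 patients per arm at baseline and week 12, and from 10 healthy subjects once.

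The section on RNA isolation and library preparation gives one line on the library: "Two to 3 μg total RNA per sample as input material is needed for cDNA library construction". It does not name the library type.

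The section on RNA-seq data processing then gives the route. Reads are "mapped to the human reference genome employing HISAT2 v2.0.4 and the aligned reads per sample will be assembled by StringTie (v1.3.3"). The expression unit follows: "Both ncRNAs and coding transcripts will be normalized and expressed as fragments per kilo-base of exon per million fragments mapped (FPKM"). The test comes next: "Differential expression will be analyzed by using Cuffdiff". Several ncRNA databases are listed in the same section, for target prediction only.

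The Mechanistic data analysis section repeats the choice of tool and lists the classes by name: "The differential expression analysis about mRNA, miRNA, lncRNA, and circRNA for all pairwise comparisons", which, for five listed contrasts, "will be performed by Cuffdiff".

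**The concern.** The article fixes a quantification and a test for noncoding RNA, and names miRNA and circRNA among the classes to be tested. Both steps were built for linear transcripts longer than a sequenced fragment. A circRNA is not linear, and a mature miRNA is not longer than a fragment.

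The noncoding work is a stated aim. The Background and Discussion describe lncRNA and circRNA in IBS-D as little studied and present the trial as the first whole-transcriptome study of the disease. Twenty patients undergo a second colonoscopy with biopsies for this outcome. If the plan is followed literally, half of the RNA classes would yield either no result or one that does not measure what its label says. The selection of RNAs for the ncRNA–mRNA networks would inherit the problem.

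**Working it through.** The article gives no figure to reproduce here. The check traces each class through the stated steps. How the tools and molecules behave is general methods knowledge, not something the article states.

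**Scope.** Profiles: (10 + 10) × 2 + 10 = 50. Class-by-contrast analyses: 4 classes × 5 contrasts = 20, of which 2 × 5 = 10 concern miRNA or circRNA.

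**mRNA and lncRNA.** Both are linear transcripts. Spliced alignment, assembly and FPKM can yield them.

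**circRNA.**
- Its defining evidence is a read that joins the end of a downstream exon to the start of an upstream one. That order is not collinear with the genome. A linear spliced aligner followed by a linear-transcript assembler does not report it.
- Its exons are shared with the linear host transcript. Let *a* be the fragments on those exons from the linear form and *b* those from the circular form. The exon-based FPKM is proportional to *a* + *b*: one observed total for two unknowns. A fall in *b* matched by a rise in *a* leaves it unchanged, and a rise in *a* alone would look like a rise in the circRNA.
- So the stated steps give either no circRNA entry, or a value that mixes in the host transcript.

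**miRNA.** Take a mature length *L* of about 22 nt (an assumption; the article gives none).
- There is nothing to assemble. The whole molecule fits in one read, and the natural measure is a read count per known miRNA.
- FPKM divides by length in kilobases. Cuffdiff uses an effective length, roughly *L* − *f* + 1, where *f* is the fragment length.
- In a library with fragments longer than the molecule (*f* > 22), 22 − *f* + 1 is zero or negative, so the scaling is undefined.
- In a small-RNA library the fragment is the molecule itself. With *f* = 22, the effective length is 22 − 22 + 1 = 1 nt and the scaling factor is 1/0.001 = 1,000. With *f* = 21, it is 2 nt and the factor is 1/0.002 = 500. A one-nucleotide difference in read length halves the reported expression at the same count.
- The measure therefore fails under either library type, and the conclusion does not depend on which one is made.

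**Search for another route.** No back-splice junction caller and no miRNA counting step appears. The databases serve target prediction. The qRT-PCR mentioned under Colonoscopy and biopsies is tied to no RNA class and is not genome-wide.

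**The case against.** The strongest defence is that this is a journal article. Library kits, circRNA callers and miRNA counting are details commonly left to a full protocol or to the sequencing vendor's procedures, and a class-specific workflow may exist there. The Mechanistic outcome section also speaks of libraries in the plural. Naming databases for miRNA and circRNA targets suggests that identification of those classes was intended. The FPKM sentence follows directly after assembly, so it could be read as covering assembled transcripts only.

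This defence would answer a complaint about silence, and the missing caller or counting step is not in itself the finding. It does not answer the explicit assignment. The statistical section names miRNA and circRNA and gives Cuffdiff as their test. If a suitable workflow exists elsewhere, these sentences contradict it and still need correcting.

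Three stronger readings are tempting, and the article does not support them:
- A reader might infer one long-RNA library in which miRNAs are lost. The library type is not given, and a small-RNA library is also a cDNA library.
- A reader might infer that the target predictions would be wrong. They are database look-ups. Expression results decide which RNAs are submitted, not whether a prediction is correct.
- A reader might expect circRNA values that silently equal host-gene expression. An empty circRNA output, which an analyst would notice, is at least as likely.

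**Conclusion.** The point holds for the plan as written. The stated quantification and test are unsuitable for circRNA and miRNA, which touches two of four classes, all 50 profiles and 10 of the 20 class-by-contrast analyses. These are counts of what is exposed, not an estimate of error. The circRNA part is the firmer: one exon-based value cannot separate two molecules that share exons. The miRNA part rests on a length of about 22 nt and on how length scaling behaves at that size.

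A reader might conclude that these classes cannot be measured in this trial at all. That does not follow. With suitable libraries and class-specific methods both can be measured, and what fails is the route that the article assigns to them. The primary, secondary and safety outcomes and the sample size are unaffected. The correction should be made before samples are processed, but it is no obstacle to the clinical comparison.

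**What to change.** - In the RNA-seq data processing and Mechanistic data analysis sections, limit HISAT2, StringTie, FPKM and Cuffdiff to mRNA and lncRNA.
- For circRNA, name a back-splice junction caller and test junction counts with a count model, provided the library is not poly-A-selected.
- For miRNA, use read counts against a miRNA reference from a small-RNA library, also tested with a count model.
- In both cases the planned Benjamini-Hochberg adjustment can stay.
- If the vendor's libraries do not support a class, remove it from the Mechanistic outcome section and from the contrasts.

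The cost is some extra bioinformatics work, or a narrower mechanistic claim. It may be more than that. For circRNA, reprocessing existing reads is enough only if the library was suitable, since a poly-A-selected one would have to be remade. A small-RNA library needs spare RNA. The article asks for 2 to 3 μg per sample from two biopsies that also serve qRT-PCR, gives no expected yield, and has the samples destroyed after use. Library type and yield should therefore be confirmed with the vendor first. No additional patient procedure is proposed.

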### Outcome measurements

#### Primary outcome

The primary outcome of our trial is the response rate of IBS-Symptom Severity Score (IBS-SSS). A responder is defined as a 50% or more reduction in IBS symptoms compared to baseline [28]. IBS-SSS is a hitherto unique symptom severity questionnaire of IBS, which evaluates the condition of abdominal pain, abdominal distension, and defecation satisfaction. This definition of a responder that reports a 50% or more reduction in IBS symptoms is less disturbed by the initial severity of IBS. IBS-SSS will be assessed at baseline, week 4, week 8, week 12, and week 20 while the response rate of IBS-SSS will be assessed at week 4, week 8, week 12, and week 20.

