### Eligibility criteria

#### Inclusion criteria

Patients have to satisfy the diagnostic criteria of IBS-D defined by ROME IV [25].The score of IBS-Symptom Severity Score (IBS-SSS) is more than 75 at baseline visit [26].Patients have to satisfy the diagnostic criteria of diarrhea syndrome with liver depression and spleen deficiency based on TCM syndrome differentiation [27].The age is between 18 and 70 years old.Patients must make an agreement to participate and sign a written informed consent.

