### Randomization and blinding

Randomization scheme that generates a list of 120-case randomization sequence utilizing the stratified block randomization method by computer will be implemented by an independent statistician, which guarantees that enrolled patients will be evenly allocated to the TXYF granule group or the placebo group. Then, 10 participants of each group will be randomly selected for RNA sequencing and whole transcriptome analysis. Concealment of allocation code relies on an opaque envelope. This trial requires that all participants and researchers involved in drug distribution, outcome evaluation, and data analysis are completely blinded to allocation. The occurrence of severe adverse events or other unpredictable events allows unblinding under the permission of the principal investigator.

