### Statistical analysis

#### Clinical data analysis

Based on the principle of intention-to-treat (ITT), all randomly assigned participants will be included in the statistical analysis. For participants who prematurely terminate this trial, outcomes of the last visit will be used as the final outcomes. Statistical analyses will be completed by SAS (version 9.4, SAS Institute, Cary, NC). Continuous variables will be presented in the form of means and standard deviations while the categorical variables will be presented in the form of counts and percentages. The primary outcome (week 4, week 8, week 12, and week 20) and the secondary outcome AR (week 12) will be assessed by using *χ*^2^ test or Fisher’s exact test. Another secondary outcome IBS-QOL (baseline, week 4, week 8, week 12, and week 20) will be assessed by using *T* test or Mann-Whitney *U* test accompanied with the Wilcoxon test. A two-sided *P* < 0.05 indicates statistical significance. For missing data, sensitivity analysis will be conducted and the optimal approach to the imputation of missing data will be proposed.

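### The primary comparison leaves out the baseline IBS-SSS, although a 50% responder rule is free of initial severity only if improvement is proportional to baseline

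*Protocol article*

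**What the plan says.** Four statements in the protocol article bear on this point.

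- **Responder rule (Primary outcome):** "A responder is defined as a 50% or more reduction in IBS symptoms compared to baseline". I read this as a fall in the IBS-SSS, since the outcome is the response rate of that score. The same section gives the reason for the rule: "This definition of a responder that reports a 50% or more reduction in IBS symptoms is less disturbed by the initial severity of IBS".
- **Entry (Inclusion criteria):** "The score of IBS-Symptom Severity Score (IBS-SSS) is more than 75 at baseline visit". No upper limit is listed.
- **Data collected (Primary outcome):** "IBS-SSS will be assessed at baseline, week 4, week 8, week 12, and week 20". The baseline score is therefore available for every eligible patient.
- **Analysis (Clinical data analysis):** the response rates at weeks 4, 8, 12 and 20 "will be assessed by using *χ*^2^ test or Fisher’s exact test". No covariate is mentioned.

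The Randomization and blinding section describes a list made "utilizing the stratified block randomization method by computer" but does not name the stratification factor. The reader cannot tell whether severity is balanced by design.

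**The concern.** The baseline IBS-SSS does three jobs here: it admits the patient, it is the denominator of the responder rule, and it is a likely predictor of response. A percentage rule removes the influence of baseline only when patients improve by a similar fraction whatever their starting score. If improvement is closer to a fixed number of points, patients who start low cross the 50% line much more easily than patients who start high. A low entry limit with no listed ceiling gives that dependence room to show.

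If response does depend on baseline, a test that ignores baseline leaves explained variation in the error term, and a chance difference in severity between the arms stays in the estimated effect. The score that would deal with both is already in the database.

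**Working it through.** **1. The plan's own figure.** Inputs from Sample size calculation: response 70% and 40%, power 80%, type I error 5%; two-sided as in Clinical data analysis. The pooled formula without continuity correction, with a mean proportion of 0.55, gives

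n = [1.96·√(2·0.55·0.45) + 0.842·√(0.7·0.3 + 0.4·0.6)]² / 0.30² ≈ (1.379 + 0.565)² / 0.09 ≈ 42 per group.

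This reproduces the stated 42. With 15% drop-out, 42/0.85 = 49.4, so 50 per group and 100 in total, also as stated. At 60 per arm the same formula gives power of 92%.

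**2. Fall needed to respond.** Required fall = baseline/2. The baselines other than the entry limit are illustrative.

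| Baseline | 76 | 100 | 175 | 300 | 400 |
|---|---|---|---|---|---|
| Required fall (points) | 38 | 50 | 87.5 | 150 | 200 |

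**3. When response does and does not depend on baseline.** Let B be the baseline and D the fall; response means D ≥ B/2.

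- *Proportional change:* D/B has the same distribution at every B, so P(D/B ≥ 0.5) is constant and the protocol's justification holds in full.
- *Additive change:* D is Normal(m, s) at every B, so P(response) = 1 − Φ((B/2 − m)/s). With assumed m = 60, s = 80, this is 61% at 76 and 13% at 300. With m = 100, s = 90, it is 75% and 29%.
- *No true change, fluctuation only:* P(response) = 1 − Φ((B/2)/SD), where SD is the assumed standard deviation of the change between visits.

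| SD of change | B = 76 | B = 150 | B = 300 |
|---|---|---|---|
| 30 | 10% | 0.6% | 0% |
| 50 | 22% | 6.7% | 0.1% |
| 70 | 29% | 14% | 1.6% |

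The protocol gives no m, s or SD and no baseline distribution, so these are ranges, not estimates.

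**4. What adjustment buys.** Two simulations with different assumptions were run.

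*Simulation A:* 3,000 trials per scenario, 60 per arm, baseline uniform on 76–400, arm response rates about 37–41% and 64–67%. An unadjusted two-proportion test is compared with a linear probability model adjusted for baseline (HC3 errors).

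| Change | Unadjusted power | Adjusted power | Difference |
|---|---|---|---|
| Additive | 87.2% | 93.1% | +5.9 |
| Mixed | 88.3% | 89.3% | +1.0 |
| Proportional | 83.7% | 82.2% | −1.5 |

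*Simulation B:* 1,500 trials per setting, marginal rates held at 40% and 70%. Chi-square is compared with logistic regression adjusted for baseline, over an assumed log-odds slope per baseline SD.

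| Slope | 42 per arm: chi-square / adjusted | 60 per arm: chi-square / adjusted |
|---|---|---|
| 0 | 81.7% / 79.7% | 92.9% / 92.7% |
| −0.5 | 83.3% / 82.9% | 93.1% / 94.3% |
| −1.0 | 81.0% / 85.2% | 91.9% / 95.5% |
| −1.5 | 82.1% / 92.4% | 92.3% / 97.5% |

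Type I error at 60 per arm was 0.049–0.055 unadjusted and 0.048–0.061 adjusted. The simulation standard error is √(0.05·0.95/1500) = 0.0056, so even the largest of these eight values lies only about two standard errors above 0.05.

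**5. Chance imbalance, additive scenario of simulation A.** Response was 77% below a baseline of 175 and 24% above 300. The midpoints of those ranges are about 125 and 350, so the slope is (77 − 24)/(350 − 125) ≈ 0.24 percentage points of response per baseline point. The baseline SD is (400 − 76)/√12 ≈ 94, and the standard error of the difference in mean baseline is 94·√(2/60) ≈ 17 points. An imbalance of one standard error then shifts the difference in response by about 0.24 × 17 ≈ 4 percentage points, against a planned difference of 30.

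**The case against.** The strongest reply is that nothing here is an error. The justifying sentence is comparative: it says the rule is disturbed less, not that it is undisturbed. A relative rule scales the required fall with baseline by design, so a 38-point fall from 76 does not contradict it. Whether the sentence is true depends on how change scales, which the protocol does not report; the section cites a source for the responder definition that is not available here. A reader might infer that the entry rule refutes the sentence and that it should go. The documents do not support that.

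A reader might also infer that the chi-square or Fisher test is biased or invalid, or that responses by fluctuation among mild patients create a false effect. They do not. Under randomisation such responses arise in both arms alike. Chance imbalance is already covered by the test's error rate, and the simulated type I error of the unadjusted test stays near 5%. The test also matches the two-proportion sample-size calculation.

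Further, the share of patients near the entry limit is unknown, the gain in power is modest, the unnamed stratification factor might be severity, and adjusted or supporting analyses are often left to an analysis plan. Simulation A did not use the logistic model proposed below, and neither simulation estimated a standardised risk difference.

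Most of this stands, and it limits the point to precision. It does not remove it. The protocol does not leave the primary comparison open: it names a test that can use neither the baseline score nor the stratification factor. If severity is the stratification factor, imbalance is reduced, but the stated test still ignores it. Simulation B did use adjusted logistic regression, and its gains at 60 per arm are of the same size as those in simulation A.

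**Conclusion.** The point holds as one of precision and wording. The 50% rule is independent of initial severity only under proportional improvement, which the protocol does not show, and the open range above 75 leaves room for response to depend on baseline. The stated primary test is valid but discards a baseline value already collected.

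The size is about 0 to 6 percentage points of power at 60 per arm, and up to about 10 at 42 per arm under the steepest slope assumed. If response does not depend on baseline there is no gain, or a loss of about 1 to 2 points. These figures rest on assumed baseline distributions, variation and slopes, because the protocol gives none.

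The evidence does not show that the justifying sentence is false, that the primary test is invalid, that the treatment effect would be biased, or that the sample size is wrong. The 42 per group reproduces and stands. The change is worth making because it is nearly free, not because the trial fails without it.

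**What to change.** - **Primary outcome:** keep the 50% definition. Qualify the justifying sentence, for example by stating that the rule is less dependent on initial severity to the extent that improvement is proportional to baseline, or give the evidence for it.
- **Clinical data analysis:** make the primary between-arm comparison of response a logistic regression with treatment, continuous baseline IBS-SSS and the randomisation stratification factor. Report it as a standardised risk difference (each patient's predicted response under both treatments, averaged, then subtracted) with a 95% CI. Keep chi-square or Fisher as a supporting analysis.
- **Randomization and blinding:** name the stratification factor, so that the model can be specified.

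The cost is wording only, to be settled before unblinding. No new data, visits or patients are needed. The model spends one degree of freedom on baseline plus those for the stratification factor, and may give up 1 to 2 points of power if change turns out to be exactly proportional.
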